**9.1.10 Immediately Reported SAEs and Other Events**

Once determining an event meets the definition of event in the study protocol, the investigator must report the event promptly as described in the table below

|  | Initial Report | | Follow-up Report | |
| --- | --- | --- | --- | --- |
| Type of Event | Time Frame | Document | Time Frame | Document |
| All SAEs | 24 hours | “SAE” information collection tool | 24 hours | Updated SAE information collection tool |
| Pregnancy | 2 weeks | Pregnancy report form | 2 weeks | Updated pregnancy form |

The methods for detecting, recording, assessing and following up AEs and SAEs and procedures for completing and submitting SAE report are provided in the SMP. The procedures for the reporting of AEs/AEs occurring after the end of study are also included.

**9.1.11 SAE Reporting Process**

For any SAEs occurring within the reporting period, the investigator must report it immediately (i.e., within a maximum of 24 hours following the awareness of the event) by phone or fax.

After the event (or follow-up information) is reported by phone, it should also be immediately reported to the Ethics Committee of Beijing Cancer Hospital, China Food and Drug administration, and the food and drug administration bureau of where the study site locates (province or city) by fax. For previously reported SAE, if any new information is available, the reporting process and time frame are the same as before (follow-up).

For the name, address, telephone number and fax number of SAE reporting, please refer to the information in the SAE report form. All written reports must be uploaded in the form of SAE report form and completed by the investigator according to the specified instructions for completion.

The investigator/reporter must timely updata follow-up information (e.g.: other information, outcome and final assessment, special records required).

Normally the clinical research associate in charge will make a request for access to follow-up information, but in special cases, the Global Drug Safety Department may contact the investigator directly to confirm, corroborate or discuss a certain important event.

The recording of SAE should specify the symptoms, severity, occurrence time, handling time, action taken, follow-up time and method, and outcome profile.

# X. Data Management and Statistical Analysis

**10.1 Completion and Transfer of Case Report Form**

The Case Report Form (CRF) will be completed by the doctor, and must be completed separately for each case enrolled. After completion, the CRF will be reviewed by the clinical research associate, and then its first copy will be transferred to the data manager for data entry and management work.

**10.2 Data Entry and Modification**

An independent data management unit will be responsible for data entry and management. To guarantee the accuracy of data, double entry and proofread should be performed by two data managers independently. For questions in the CRF, the data manager will fill out a Data Request Queue (DRQ), and send a query to the investigator via the clinical research associate, to which the investigator should answer the questions and reply as soon as possible, and then the data manager will carry out data modification, confirmation and entry according to the investigator’s answer, and if necessary, send a DRQ again.

**10.3 Statistical Analysis of Trial Data**

All the data will be statistically analyzed and reported using R ver. 3.6.1 software. All patients who have received at least one therapeutic dose will be included in the descriptive safety analysis. Safety analysis: predominantly descriptive statistical analysis.

# XI. Study Management

**1. Case Report Form**

The primary purpose is to obtain information required by the study protocol in a complete, accurate, clear and timely manner. The data in the CRF should be consistent with those in the source documents. The CRF must be completed in a complete and legible manner (using black or blue ball pain, complying with the requirements in regulatory documents).

All revisions and corrections must be done and confirmed by the investigator, with the date of revision/correction specified. Mistakes must be retained clearly and not overwritten with corrected data (e.g., using correction fluid). The investigator must indicate the reason for revising important information.

For missing information/annotation in the medical record, their space input in the CRF should be substituted by line-drawing cancellation to avoid unnecessary follow-up investigation.

The CRF is a regulatory document and must be appropriate for submission to the hospital authorities.

**2. Study File and Preservation**

The investigator should have a file concerning the study objective. This file should contain all related documents required for conducting the study. After the end of the study, these documents should be archived according to relevant regulations of the hospital and the country.

**3. Regulations on Data Management and Data Traceability**

The CRF will be completed by the investigator and must be completed separately for each enrolled subject. After completion, the CRF will be reviewed by the clinical research associate, and then transferred to the data manager for double data entry and data management work.

During this period, query forms may be transferred by the clinical research associate to the investigator for data review, the investigator should answer the queries and return the form so soon as possible. It is not allowed to modify locked data documents. The database will be transferred to the statistical analysis personnel, who will then carry out statistical analysis according to the requirements in the statistical plan. The statistical analysis report will be given to the principal investigator of this trial for writing the study report.

The investigator will be trained on relevant laws and regulations and SOP, and all investigators are required to strictly abide by such laws and regulations and SOP, so as to ensure the data are recorded in an authentic, timely, accurate and complete manner and prevent omission and arbitrary modification, data falsification and data fabrication; the clinical research associate should strengthen the verification of various records. Subject’s follow-up medical record is one of the source documents and should be preserved together with the CRF. The laboratory department of each site provides the quality control certification granted by the National Center for Clinical Laboratories, and the laboratory results will be preserved in the computer connected to the test equipment for at least three years for further reference.

**4. Quality Control and Quality Assurance of Clinical Trial**

Both the sponsor and investigator should perform their respective duties, strictly follow the clinical trial protocol, and adopt standard operating procedures to guarantee the implementation of the quality control and quality insurance system of the clinical trial.

All related observations and findings in the clinical trial should be verified and each stage of data processing must be performed with quality control to ensure the completeness, accuracy, authenticity and reliability of data.

This study is subject to systemic inspection by drug regulatory agencies and sponsor’s authorized inspector on the related activities and documents of this clinical trial to evaluate if this trial is conducted in accordance with the trial protocol, standard operating procedures and relevant regulatory requirements and if the trial data are recorded in a timely, authentic, accurate and complete manner. The inspection should be executed by personnel not directly involved in this clinical trial.

This study is subject to the inspection by drug regulatory agencies on the respective duties of the investigator and sponsor in implementing this trial and fulfillment of such duties.

**5. Other Regulations**

The CRF will be completed by the investigator and must be completed separately for each case enrolled. After completion, the CRF will be reviewed by the clinical research associate, and then transferred to the data manager for data entry and management work.

# XII. Ethics and Laws and Regulations

**1. Investigator’s Responsibilities**

The investigator should be responsible for ensuring that the clinical study is conducted in accordance with the study protocol and that the ethical principles in the Declaration of Helsinki (World Medical Association Declaration of Helsinki, current revised version) and Good Clinical Practice (GCP) with appropriate modifications in line with China's actual conditions. Subject-related materials and specimens will be preserved in Beijing Cancer Hospital, scientific and standard information management and specimen collection will be carried out by the investigator and professional personnel, and only the investigator, Ethics Committee and drug regulatory agencies will be given access to related medical records. After the end of the study, related specimens will be disposed of according to the hospital’s routine process. Any public reports concerning the results of this study will not disclose subject’s personal identity. We will make every effort to protect subject’s personal medical information privacy to the extent permitted by law. The above documents must be expounded in the subject’s ICF, which is the essential prerequisite for clinical study enrollment.

**2. Subject Information**

Signing the written ICF is the essential prerequisite for a patient to be enrolled. Before the signature, the investigator must provide subjects with sufficient information. If in compliance with the hospital’s regulations, the investigator may designate a person to provide subjects with such information. Besides from the provision of written information, the investigator or designee should also verbally inform the patients. Attention should be paid to the selection of wording, so that subjects can fully and easily understand the information.

Whenever any new important information involving patient’s informed consent is found, the subject information form should be modified accordingly.

**3. ICF**

Before any study-related behavior is conducted, there must be a written consent form on patient’s voluntary participation in the clinical trial. The ICF should be signed by the patient and the investigator or his/her designee in person, with the date of signature indicated.

The investigator should confirm in the CRF again whether a consent form is signed. The signed and dated ICF should be preserved at the study site and archived safely by the investigator for supervision, review and inspection at any time.

An original copy of the ICF should be given to patients before the conduct of the study.

If a patient or his/her legal representative is not able to read the ICF, a reliable, independent witness should attend the entire process of ICF discussion. The selection of witness must guarantee the patient’s right to confidentiality. The reliable, independent witness should be an independent individual instead of personnel affiliated to the study institution or participating in the study. Family members or acquaintances are good choice for independent witness. If possible, after the subject or patient or his/her legal representative gives verbal consent and signs the ICF, the witness should sign and date the ICF in person to prove the information is correct, since only when the patient or his/her legal representative fully understands the contents of the ICF can the ICF be authentic.

**4. Ethics Committee**

Before the initiation of the study, the study protocol and related documents (e.g., patient information, ICF, Investigator’s Brochure, etc.) should be submitted together to the Ethics Committee for approval. Study documents accepted/approved by the Ethics Committee should be archived. The study can only be conducted after a written approval is obtained.

Any amendment to the study protocol should be submitted to the Ethics Committee, and SAEs should be reported to IRB according to international and/or local requirements.

# XIII. Study Period

The trial is reviewed and approved by the Ethics Committed in May 2019 and is initiated in May 2019;

The trial will be ended in May 2022.

**Annex 1 Performance Status Score**

ECOG-Zubrod-WHO Performance Status Score Scale

| Grade | Performance Status | Equivalent to Karnofsky Performance Status |
| --- | --- | --- |
| 0 | Fully active, able to carry on all pre-disease performance without restriction. | 90-100 |
| 1 | Restricted in physically strenuous activity but ambulatory and able to carry out work of a light or sedentary nature, e.g., light house work, office work. | 70-80 |
| 2 | Tolerable to tumor symptoms, ambulatory and capable of all selfcare but unable to carry out any work activities; up and about more than 50% of waking hours | 50-60 |
| 3 | Severe symptoms of tumor; confined to bed or chair more than 50% of waking hours, but able to get out of bed and stand, capable of only limited selfcare | 30-40 |
| 4 | Totally confined to bed or chair; cannot carry on any selfcare | 10-20 |
| 5 | Dead | 0 |

**Annex 2 Response Evaluation Criteria in Solid Tumors (RECIST)**

Definitions

Measurable disease – the presence of at least one measurable lesion. If the measurable disease is restricted to a solitary lesion, its neoplastic nature should be confirmed by cytology/histology.

Measurable lesion – lesions that can be accurately measured in at least one dimension with longest diameter ≥20 mm using conventional techniques or ≥10 mm by spiral CT scan.

Non-measurable lesions – all other lesions, including small lesions (longest diameter <20 mm with conventional techniques or <10 mm with spiral CT scan), i.e., bone lesions, leptomeningeal disease, ascites, pleural/pericardial effusion, inflammatory breast disease, lymphangitis cutis/pulmonis, cystic lesions, and also abdominal masses that are not confirmed and followed by imaging techniques.

- All measurements should be taken and recorded in metric notation, using a ruler or calipers. All baseline evaluations should be performed as closely as possible to the beginning of treatment and never more than 4 weeks before the beginning of treatment.
- The same method of assessment and the same technique should be used to characterize each identified and reported lesion at baseline and during follow-up.
- Clinical lesions will only be considered measurable when they are superficial (e.g., skin nodules and palpable lymph nodes). For the case of skin lesions, documentation by color photography, including a ruler to estimate the size of the lesion, is recommended.

Methods of measurement

- CT and MRI are the best currently available and reproducible methods to measure target lesions selected for response assessment. Conventional CT and MRI should be performed with cuts of 10 mm or less in slice thickness contiguously. Spiral CT should be performed using a 5 mm contiguous reconstruction algorithm. This applies to tumors of the chest, abdomen and pelvis. Head and neck tumors and those of extremities usually require specific protocols.
- Lesions on chest X-ray are acceptable as measurable lesions when they are clearly defined and surrounded by aerated lung. However, CT is preferable.
- When the primary endpoint of the study is objective response evaluation, ultrasound (US) should not be used to measure tumor lesions. It is, however, a possible alternative to clinical measurements of superficial palpable lymph nodes, subcutaneous lesions and thyroid nodules. US might also be useful to confirm the complete disappearance of superficial lesions usually assessed by clinical examination.
- The utilization of endoscopy and laparoscopy for objective tumor evaluation has not yet been fully and widely validated. Their uses in this specific context require sophisticated equipment and a high level of expertise that may only be available in some centers. Therefore, the utilization of such techniques for objective tumor response should be restricted to validation purposes in specialized centers. However, such techniques can be useful in confirming complete pathological response when biopsies are obtained.
- Tumor markers alone cannot be used to assess response. If markers are initially above the upper normal limit, they must normalize for a patient to be considered in complete clinical response when all lesions have disappeared.
- Cytology and histology can be used to differentiate between PR and CR in rare cases (e.g., after treatment to differentiate between residual benign lesions and residual malignant lesions in tumor types such as germ cell tumors).

Baseline documentation of “target” and “non-target” lesions

- All measurable lesions up to a maximum of 5 lesions per organ and 10 lesions in total, representative of all involved organs should be identified as target lesions and recorded and measured at baseline.
- Target lesions should be selected on the basis of their size (lesions with the longest diameter) and their suitability for accurate repeated measurements (either by imaging techniques or clinically).
- A sum of the longest diameter (LD) for all target lesions will be calculated and reported as the baseline sum LD. The baseline sum LD will be used as reference by which to characterize the objective tumor response.
- All other lesions (or sites of disease) should be identified as non-target lesions and should also be recorded at baseline. Measurements of these lesions are not required, but the presence or absence of each should be noted throughout follow-up.

Response criteria

| Evaluation of target lesion |  |
| --- | --- |
| Complete response (CR): | Disappearance of all target lesions. |
| Partial response (PR): | At least a 30% decrease in the sum of the LD of target lesions, taking as reference the baseline sum LD. |
| Progressive disease (PD): | At least a 20% increase in the sum of the LD of target lesions, taking as reference the smallest sum LD recorded since the treatment started or the appearance of one or more new lesions. |
| Stable disease (SD): | Neither sufficient shrinkage to qualify for PR nor sufficient increase to qualify for PD, taking as reference the smallest sum LD since the treatment started. |

Evaluation of non-target lesions

| Complete response (CR): | Disappearance of all non-target lesions and normalization of tumor marker level. |
| --- | --- |
| Incomplete response or stable disease (SD): | Persistence of one or more non-target lesion(s) or/and maintenance of tumor marker level above the normal limits. |
| Progressive disease (PD): | Appearance of one or more new lesions and/or unequivocal progression of existing non-target lesions. Although an unequivocal progression of existing “non-target” lesions is exceptional, in such circumstances, the opinion of the treating physician should prevail and the progression status should be confirmed later on by the review panel (or study chair). |

Evaluation of best overall response

The best overall response is the best response recorded from the start of the treatment until disease progression/recurrence (taking as reference for PD the smallest measurements recorded since the treatment started). In general, the patient’s best response assignment will depend on the achievement of both measurement and confirmation criteria.

| Target lesions | Non-target lesions | New lesions | Overall response |
| --- | --- | --- | --- |
| CR | CR | No | CR |
| CR | Non-CR/SD | No | PR |
| PR | Non-PD | No | PR |
| SD | Non-PD | No | SD |
| PD | Any | Yes or No | PD |
| Any | PD | Yes or No | PD |
| Any | Any | Yes | PD |

- Patients with a global deterioration of health status requiring discontinuation of treatment without objective evidence of disease progression at that time should be classified as having “symptomatic deterioration”. Every effort should be made to document the objective progression even after discontinuation of treatment.
- In some circumstances it may be difficult to distinguish residual disease from normal tissue. When the evaluation of complete response depends on this determination, it is recommended that the residual lesion be investigated (fine needle aspirate/biopsy) to confirm the complete response status.
- Confirmation.
- The main goal of confirmation of objective response is to avoid overestimating the response rate observed. In cases where confirmation of response is not feasible, it should be made clear when reporting the outcome of such studies that the responses are not confirmed.
- To be assigned a status of PR or CR, changes in tumor measurements must be confirmed by repeat assessments that should be performed no less than 4 weeks after the criteria for response are first met. Longer intervals as determined by the study protocol may also be appropriate.
- In the case of SD, follow-up measurements must have met the SD criteria at least once after study entry at a minimum interval (in general, not less than 6-8 weeks) that is defined in the study protocol.
- Duration of overall response.
- The duration of overall response is measured from the time measurement criteria are met for CR or PR (whichever status is recorded first) until the first date that recurrence or PD is objectively documented, taking as reference for PD the smallest measurements recorded since the treatment started.
- Duration of stable disease
- SD is measured from the start of the treatment until the criteria for disease progression are met, taking as reference the smallest measurements recorded since the treatment started.
- The clinical relevance of the duration of SD varies for different tumor types and grades. Therefore, it is highly recommended that the protocol specifies the minimal time interval required between two measurements for determination of SD. This time interval should take into account the expected clinical benefit that such a status may bring to the population under study.
- Response review.
- For clinical trials where the response rate is the primary endpoint it is strongly recommended that all responses be reviewed by an expert(s) independent of the study at the study’s completion. Simultaneous review of the patients’ files and radiological images is the best approach.
- Reporting of results.
- All patients included in the study must be assessed for response to treatment, even if there are major trial protocol treatment deviations or if they are ineligible. Each patient will be assigned one of the following categories: 1) complete response, 2) partial response, 3) stable disease, 4) progressive disease, 5) early death from malignant disease, 6) early death from toxicity, 7) early death because of other cause, or 9) unknown (not assessable, insufficient data).
- All of the patients who met the eligibility criteria should be included in the main analysis of the response rate. Patients in response categories 4-9 should be considered as failing to respond to treatment (disease progression). Thus, an incorrect treatment schedule or drug administration does not result in exclusion from the analysis of the response rate. Precise definitions for categories 4-9 will be protocol specific.
- All conclusions should be based on all eligible patients.
- Sub-analyses may then be performed on the basis of a subset of patients, excluding those for whom major protocol deviations have been identified (e.g., early death due to other reasons, early discontinuation of treatment, major protocol violations, etc.). However, these sub-analyses may not serve as the basis for drawing conclusions concerning treatment efficacy, and the reasons for excluding patients from the analysis should be clearly reported.
- The 95% confidence intervals should be provided.

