# Synopsis of the Study Protocol

| Study Title | A Phase II Clinical Study to Evaluate the Efficacy and Safety of Afatinib for Pretreated Patients with Advanced Esophageal Squamous Cell Carcinoma with EGFR Overexpression/Amplification |
| --- | --- |
| Study Objective | To explore the efficacy and safety of afatinib as the second-line or beyond therapy for advanced esophageal squamous cell carcinoma (ESCC) with EGFR overexpression/amplification |
| Trial Site | Peking University Cancer Hospital and Institute |
| Trial Design | A non-randomized, open-label, single-arm clinical study. Subjects receive afatinib (40 mg po. Qd) in 4-week cycles until disease progression, occurrence of intolerable toxicity, loss to follow-up or death, or other situations in which the investigator determines the treatment should be discontinued. |
| Number of Subjects | 40 |
| Study Endpoints | Primary study endpoint: Objective response rate (ORR)  Secondary study endpoints: Disease control rate (DCR), safety, progression Free Survival (PFS) and overall survival (OS)  Exploratory endpoint: Quality of life, efficacy markers |
| Study Duration | First Patient In Time (FPI): 05/2019  Last Patient In Time (LPI): 05/2020 |
| Inclusion Criteria | 1. Voluntarily participating and signing the Informed Consent Form; 2. Age: 18 to 70 years of age; 3. Male or female; 4. Pathologically confirmed ESCC; 5. Pathologically confirmed immunohistochemical EGFR (3+) or EGFR-FISH amplification or EGFR amplification by NGS-testing (see Annex 4 for specific testing standards) 6. Radiographically confirmed unresectable advanced ESCC; 7. Failure of the first-line or beyond therapy; 8. At least one measurable lesion (per RECIST 1.1 criteria), with the imaging diagnosis ≤ 21 days apart from the enrollment time; 9. Life expectancy of ≥ 3 months; 10. General performance status (ECOG) score of 0-2; 11. Sufficient bone marrow hematopoiesis (within 7 days): hemoglobin ≥ 9 g/dL, white blood cell ≥ 3.0 × 10^9^/L, neutrophil ≥ 1.5 × 10^9^/L, platelet ≥ 100 × 10^9^/L; normal hepatic and renal functions (within 14 days): TBIL ≤ 1.5 × upper limit of normal (ULN); ALT and AST ≤ 2.5 × ULN, or ≤ 5 × ULN in the presence of liver metastasis; creatinine ≤ 1.5 × ULN; 12. Cardiac, pulmonary, renal and hepatic functions are basically normal; |

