## (II) Exclusion Criteria

1. Patients who are currently receiving other effective treatment regimens;
2. Participation in other clinical trials within 4 weeks prior to enrollment;
3. Inability to cooperate in oral administration of afatinib;
4. No measurable tumor lesion, for example, body cavity fluid or diffuse organ infiltration;
5. Prior radiotherapy on the measurable lesion;
6. Prior use of anti-EGFR targeted therapy;
7. Coexistence of other primary malignancies other than esophageal cancer, excluding cured basal cell carcinoma of skin and cervical carcinoma in situ;
8. Clinically significant cardiovascular diseases such as heart failure (NYHA class III-IV), uncontrolled coronary heart disease, cardiomyopathy, arrhythmia, uncontrolled hypertension, or history of myocardial infarction within the past 1 year;
9. Nervous or mental disorders affecting the cognitive ability, including central nervous system metastasis;
10. Severe active clinical infection (at grade >2 per NCI-CTCAE Version 4.0) including active tuberculosis within 14 days prior to enrollment;
11. Known or self-complained HIV infection or active hepatitis B or hepatitis C;
12. Uncontrolled systemic diseases such as poorly uncontrolled diabetes mellitus;
13. History of interstitial lung disease such as interstitial pneumonia and pulmonary fibrosis, or chest X-ray/CT evidence of interstitial lung disease at baseline;
14. Keratitis, ulcerative keratitis or severe xerophthalmia;
15. Known hypersensitivity or allergic reaction to any component of the investigational drug;
16. Pregnancy (confirmed by serum β-chorionic gonadotrophin test) or lactation;

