## (III) Removal Criteria

1. Non-compliance with inclusion criteria;
2. Patients who violate the requirements of the study protocol, fail to take medicines as required and fail to complete the plan;
3. Poor quality of data recording, and incomplete and inaccurate data.
4. Use of other antitumor drug therapy during the clinical study period.

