**2. Prohibited Medications**

During the study, subjects are not allowed to use Chinese medicines with an antitumor effect indicated in the package insert; and not allowed to receive concomitant, long-term systemic immunotherapy, chemotherapy, radiotherapy (except palliative radiotherapy), hormonal therapy for treatment of tumors (however, glucocorticoids for antiemetic purpose and progestogen for tumor cachexia are exceptions), or other investigational drugs.

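### The protocol does not settle how a patient who takes another antitumor drug before progression counts in the primary response rate: Annex 2 sets no cut-off and retains the patient, while the removal criteria take the patient out

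*Protocol*

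**What the plan says.** The Synopsis makes ORR (CR plus PR by RECIST) the primary endpoint and DCR a secondary one. Four places bear on a patient who takes another antitumor drug before progression.

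- **Annex 2, best overall response:** "The best overall response is the best response recorded from the start of the treatment until disease progression/recurrence". Progression or recurrence is the only closing event. For patients who stop treatment because their health deteriorates without documented progression, the annex adds: "Every effort should be made to document the objective progression even after discontinuation of treatment".
- **Annex 2, reporting of results:** "All of the patients who met the eligibility criteria should be included in the main analysis of the response rate". It goes on to say that faulty treatment or dosing is no ground for exclusion, and that analyses leaving out protocol violators cannot support efficacy conclusions.
- **Section IV (III), Removal Criteria, item 4:** "Use of other antitumor drug therapy during the clinical study period". No class or duration limit is given. The section does not say whether removal is from treatment, from the study or from the analysis.
- **Section VII (IV), Prohibited Medications:** patients are "not allowed to receive concomitant, long-term systemic immunotherapy, chemotherapy, radiotherapy (except palliative radiotherapy), hormonal therapy for treatment of tumors", nor other investigational drugs. The same sentence also says that "subjects are not allowed to use Chinese medicines with an antitumor effect indicated in the package insert". Marketed targeted agents are not named.

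**The concern.** With no control arm, a response can be attributed to afatinib only if afatinib is the sole active antitumor treatment up to the scan that counts. The protocol lets afatinib stop without progression. Section IV (IV) lists toxicity, a delay of 14 days or more, poor compliance, investigator judgement and patient request. Another therapy can therefore begin while the response window is still open.

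The protocol then gives two incompatible instructions. Following Annex 2, the patient stays in and nothing separates shrinkage before the switch from shrinkage after it. Following the removal criterion, the patient may drop out of the ORR calculation because of something that happened after enrolment. The decision rule turns on a small count, 8 responses among 40 patients, so one or two such patients can change the conclusion.

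**Working it through.** **1. The passages side by side.** Take a patient who stops afatinib without progression and starts another antitumor drug.

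| Source | In the ORR denominator? | Can a later response count? |
|---|---|---|
| Annex 2, best overall response | Not addressed | Yes, until progression |
| Annex 2, reporting of results | Yes, if eligible | Not addressed |
| Removal criterion 4 | No, if removal means from the analysis | No, on that reading |

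The second and third rows cannot both be followed. The first adds no cut-off that would make retention safe.

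**2. The plan's own design.** Inputs from the Synopsis: p0 = 0.10, p1 = 0.25, n1 = 22, R1 = 2, N = 40, R2 = 8, α = 0.05, power 0.8. The exact two-stage probability of success is

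P(success | p) = Σ over x1 ≥ 3 of P(X1 = x1) × P(X2 ≥ 8 − x1), with X1 ~ Bin(22, p) and X2 ~ Bin(18, p).

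- p = 0.10 gives 0.0398.
- p = 0.25 gives 0.803.

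The stated design is reproduced when R2 = 8 is read as the smallest number of responses for success. That reading is used below.

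**3. If Annex 2 governs and the patient is retained.** Let s be the share of afatinib non-responders who switch before progression, and q the ORR of the other drug. Suppose every response to that drug is scanned, confirmed and credited. The apparent ORR is then 0.10 + 0.90 × s × q. The protocol gives neither s nor the ORR of any particular later drug. For q, 12.8% is the second-line ORR in the Background section; 25% and all values of s are assumptions.

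| s | q | Apparent ORR | P(success) |
|---|---|---|---|
| 0 | – | 0.100 | 0.040 |
| 5% | 12.8% | 0.10 + 0.90 × 0.05 × 0.128 = 0.1058 | 0.053 |
| 10% | 12.8% | 0.1115 | 0.068 |
| 20% | 12.8% | 0.1230 | 0.106 |
| 20% | 25% | 0.1450 | 0.207 |

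A separate way to see the sensitivity is to suppose that exactly one non-responder in stage 2 is wrongly credited. Stage 1 still needs 3 genuine responses, but the total needs only 7. Replacing 8 by 7 in the formula gives 0.090 at p = 0.10. Each such response adds 1/40 = 2.5 percentage points to the observed ORR.

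**4. If the removal criterion governs and the patient is dropped.** The direction depends on who is dropped. With counts chosen only to show this:

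- 7/40 = 17.5%. Dropping two non-responders who switched gives 7/38 = 18.4%, which is higher.
- 8/40 = 20.0%. Dropping one patient who had responded to afatinib before switching gives 7/39 = 17.9%, which is lower.

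In both cases fewer than 40 patients remain, so the boundary of 8 no longer applies to the sample size it was calculated for.

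**The case against.** The strongest counter-argument is that the protocol already deals with other antitumor drugs. Removal criterion 4 has no class or duration limit, it stands in the body of the protocol, and Annex 2 is a general RECIST excerpt that in places defers to the protocol. Nothing need be credited to afatinib if that criterion means exclusion from the analysis. A reader might infer that best response is counted whatever other treatment is given; the documents do not support that, because of this criterion. What remains is that removal is undefined, that the protocol never says which text prevails, and that exclusion would create the denominator problem.

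Second, the route to a miscredited response is narrow. CR and PR need a repeat assessment at 4 weeks or later (Section V (II) footnote; Annex 2), so a single scan showing 30% shrinkage is not enough. Imaging is scheduled only among the assessments during study treatment. The sentence on seeking progression after discontinuation concerns symptomatic deterioration, not patients who stop for toxicity. This lowers the likely frequency. It does not remove the route, because Annex 2 does not disqualify an off-treatment scan, and confirmation says nothing about which drug caused the shrinkage.

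Third, a reader might take the prohibited list to ban only prolonged systemic therapy. That is one reading. The qualifier may attach to immunotherapy alone, and the bans on antitumor Chinese medicines and investigational drugs do not carry it.

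Fourth, a cut-off at subsequent therapy is often left to the SAP, which is not shown. Its absence alone would be no finding. The conflict between the removal criterion and Annex 2 is in the protocol itself.

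**Conclusion.** The point holds as an unresolved contradiction in how the primary endpoint is counted. The removal criteria and the Annex 2 reporting rules give opposite answers for a patient who takes another antitumor drug before progression, and the best-response definition has no cut-off to protect attribution if the patient is kept.

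The documents do not show that ORR will be inflated. Bias is upward only if such patients are retained, rescanned and confirmed as responders; under removal it can go either way. The size cannot be estimated without a switching rate. The mild illustration (5% switching, 12.8% ORR, true afatinib ORR 10%) moves the false-positive probability from 4.0% to 5.3%. The 9.0% figure takes one false stage 2 response as given, and the values above 10% need heavier switching (20% of non-responders at an ORR of 12.8%) or a more active second drug. The case for correcting the text rests on the contradiction and on the small count that decides the trial, not on any one of these figures.

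**What to change.** Add an endpoint definition to the body of the protocol. For ORR and DCR, best overall response is the best response recorded, confirmed for CR and PR, from the start of treatment until progression or the start of any other antitumor therapy, whichever comes first. Keep all eligible treated patients in the denominator, and state that removal criterion 4 does not take a patient out of the ORR analysis. A patient who switches is then judged only on earlier scans.

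Separately, the sponsor must reconcile removal criterion 4 with the prohibited-medication section. They describe other antitumor therapy differently: the second does not name marketed targeted agents, and the reach of its long-term qualifier is unclear. Which therapies are allowed is for the sponsor to decide.

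The cost is a few sentences of protocol text, with no extra visits or patients. The downside is that a response arising after a switch no longer counts, so the reported ORR may be slightly lower.
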